## Abstract

**Background:**

Stroke is a leading cause of adult disability and mortality. Intravenous thrombolysis can minimize disability when patients present to the emergency department for treatment within the 3 − 4½ h of symptom onset. Blacks and Hispanics are more likely to die and suffer disability from stroke than whites, due in part to delayed hospital arrival and ineligibility for intravenous thrombolysis for acute stroke. Low stroke literacy (poor knowledge of stroke symptoms and when to call 911) among Blacks and Hispanics compared to whites may contribute to disparities in acute stroke treatment and outcomes. Improving stroke literacy may be a critical step along the pathway to reducing stroke disparities. The aim of the current study is to test a novel intervention to increase stroke literacy in minority populations in New York City.

**Design and Methods:**

In a two-arm cluster randomized trial, we will evaluate the effectiveness of two culturally tailored stroke education films – one in English and one in Spanish – on changing behavioral intent to call 911 for suspected stroke, compared to usual care. These films will target knowledge of stroke symptoms, the *range of severity* of symptoms and the therapeutic benefit of calling 911, as well as address barriers to timely presentation to the hospital. Given the success of previous church-based programs targeting behavior change in minority populations, this trial will be conducted with 250 congregants across 14 churches (125 intervention; 125 control). Our proposed outcomes are (1) recognition of stroke symptoms and (2) behavioral intent to call 911 for suspected stroke, measured using the Stroke Action Test at the 6-month and 1-year follow-up.

**Discussion:**

This is the first randomized trial of a church-placed narrative intervention to improve stroke outcomes in urban Black and Hispanic populations. A film intervention has the potential to make a significant public health impact, as film is a highly scalable and disseminable medium. Since there is at least one church in almost every neighborhood in the USA, churches have the ability and reach to play an important role in the dissemination and translation of stroke prevention programs in minority communities.

**Trial registration:**

NCT01909271; July 22, 2013

## Background

### Introduction

Stroke is the leading cause of adult disability, with an estimated 795,000 new and recurrent strokes occurring annually in the US [1,2]. Stroke is also among the most economically burdensome conditions, costing US taxpayers > $60 billion annually [1,2]. Furthermore, stroke is a significant contributor to health inequities. In comparison to Whites, Blacks are at least twice as likely to die from stroke, and they have a four-fold higher incidence of first-ever stroke, particularly among those aged 34-55 years [3].

The administration of intravenous thrombolytic therapy with tissue plasminogen activator (t-PA) following an ischemic stroke can reduce the patient’s disability by 31-50% [4]. However, the narrow 3 − 4½ h treatment window is a critical limitation on the effectiveness of treatment with t-PA [4,5]. Currently, only 3-5% of diagnosed ischemic stroke events receive t-PA therapy. This low rate of treatment is predominantly due to the public’s inability to identify and respond appropriately to stroke symptoms when they occur [6]. Stroke education studies have shown that placing an emphasis on calling 911 for suspected stroke can lead to reduced pre-hospital delays [4] and increased thrombolysis for acute stroke [7].

The cascade of events and behavioral responses that occur in the pre-hospital setting of acute stroke include: (1) the *onset* of stroke-like symptoms, (2) the *recognition* of those symptoms by the patient, family or observer, (3) the *perception* of stroke-like symptoms as symptoms that warrant immediate medical attention, (4) the decision to seek medical attention, and (5) the choice of transportation to the emergency department (ED) (i.e., calling 911 for an ambulance versus an alternative mode of transportation) [8]. The *onset* of symptoms may not always correspond to the *recognition* of the symptoms, with the former influencing the consideration of t-PA therapy and the latter influencing the likelihood of seeking medical attention.

In a review of 182 stroke education studies, we found that there is a discrepancy between knowledge concerning stroke symptoms and the reaction to an acute manifestation of one or more of these symptoms [9]. Mass media campaigns have had some success in increasing the public’s knowledge of stroke symptoms, but have provided little evidence that such knowledge is related to help-seeking behaviors [10]. At the core of the problem is the relationship among three elements, (1) the recognition of any one cardinal stroke symptom, (2) the perceived severity of the symptom, and (3) the ambiguity of the situation that may determine one’s action – to call or not to call 911. At high levels of perceived severity, the specific recognition of a particular symptom is less important than at low levels. For example, when one experiences weakness in one side of his body, such that he is no longer able to stand up, or witnesses such in another person, the situation is unambiguous and a call to 911 is clearly warranted. In contrast, when a symptom is perceived to have low severity or transiency (e.g., mild focal weakness, numbness or transient monocular blindness), ambiguity is greater and the likelihood of calling 911 is diminished. This remains the case even if that person is aware that such deficits can be a stroke symptom [11]. However, it is recommended that the recognition of a symptom, even at a very low level of perceived severity and the resultant ambiguity, result in a call to 911.

### Stroke disparities

Despite higher stroke incidence rates compared to Whites, Blacks and Hispanics are less likely to use ambulance services, which is associated with delayed arrival at the ED and ineligibility for intravenous thrombolysis for acute stroke [12]. This delay in immediate presentation in the ED is largely dependent on patients’ recognition of stroke symptoms and their urgency [5]. In previous studies, our group has found very low stroke literacy rates – which we define as knowledge of stroke symptoms and when to call 911 for suspected stroke – among Blacks and Hispanics compared to Whites [13-17]. These findings may, in part, be responsible for disparities in acute stroke treatment rates [11]. Increasing stroke literacy may be an effective means for improving recognition of symptoms and the need for an urgent response. This latter component – emphasis on *urgent action* in response to stroke symptoms (i.e., calling 911 and getting to the hospital) – is a critical component of stroke symptom recognition required for appropriate action that may increase use of thrombolytic therapy [9]. Thus, novel interventions that address the *perception of severity of symptoms as urgent* – a subtlety that has been often overlooked by previous stroke educational interventions – are needed.

### Narrative persuasion

In this study, we will build on our previous work that identified barriers to increasing stroke literacy and behavioral intent to call 911 for acute stroke [11,18]. With a focus on Black and Hispanic populations in New York City, we developed and pilot-tested a novel, culturally tailored intervention that uses storytelling and narrative persuasion to increase stroke literacy, in the form of two professionally produced films – one in English and one in Spanish (Figure 1).

**Figure 1 Fig1:**
[figure not shown]
English and Spanish short stroke films.

Narrative approaches, which include stories, drama, personal experience and the experience of others, may be especially effective among populations with a strong oral tradition [19]. Early Black Americans learned about their culture, their contributions to human civilization and strategies for surviving adversity through the lens of orally handed down stories [20]. Building on this tradition, the use of culturally tailored narrative approaches to health communication may be a novel method for stroke-related health communication [21]. Narrative persuasion has been shown to lower blood pressure in African Americans with hypertension [22] and improve decision-making regarding prostate cancer screening of patients with low health literacy [23]. Narrative approaches may also play a significant role in health behavior interventions targeting Hispanics. Spanish-language video narratives known as *telenovelas* have been shown to increase breast cancer knowledge, positively influence attitudes toward breast cancer screening [24], positively influence attitudes toward substance use prevention [25], and increase HIV awareness and testing [26,27].

In this study, Tailored Approaches to Stroke Health Education (TASHE), we will evaluate the effectiveness of our narrative film intervention on increasing stroke literacy in 250 individuals (125 intervention; 125 control) from 14 churches at the 6-month and 1-year follow-up. Churches are among the most credible institutions within most communities and play a particularly influential role in African-American and most Hispanic cultures. They also provide access to groups that convene regularly and are a valuable delivery channel for health promotion programs. Additionally, oral narratives are a critical component of religious communication, making church congregants a potentially receptive audience for experiential storytelling [28]. Several studies have supported a church-based approach to health behavior interventions for Black and Hispanic communities, including stroke reduction in at-risk populations [29-39].

## Methods

### Study design overview

TASHE is a two-phase study design. In the first phase, we developed two 12-min, culturally tailored, theatrical films about stroke – English and Spanish versions. The films were designed to increase stroke literacy, with a focus on behavioral intent to call 911. The second phase is a two-arm cluster randomized trial in which we will evaluate the effectiveness of the intervention films, compared to the usual practice (Usual Care) of distributing stroke education brochures to lay people, in improving stroke literacy in churches located in Black and Hispanic communities. This study has received ethics approval from the Columbia University Medical Center Institutional Review Board (IRB-AAAK5853).

### Community action plan

A Community Advisory Committee (CAC) of church pastors, other key church personnel and stroke survivors was established to work with an overarching transdisciplinary group that includes the study leadership, a health communication expert and the film producer, for the purpose of assisting with tailoring the stroke film production to meet the spiritual, cultural and educational needs of their congregations. In addition to helping with the development of the intervention, the CAC will meet with the study staff to discuss and provide ongoing feedback on the delivery of the intervention throughout the course of the study. Once analyses are completed, the process evaluation and outcomes will be reviewed with the CAC to garner their opinions on the meaning of the findings for their community and co-develop mechanisms for dissemination.

### Film development

Five focus groups conducted with stroke survivors (*N* = 31) in New York City helped inform film development. Three groups were conducted in English and two in Spanish. The focus groups were held in churches and community centers that were centrally located and handicapped accessible. Two experienced researchers facilitated the groups using a semi-structured, open-ended interview guide. Individual follow-up interviews were conducted with select participants when the story seemed to have more depth that could be explored or when further clarity was needed.

The focus groups and interviews were recorded and transcribed verbatim. Data were analyzed using content analysis techniques [40] and coded using Atlas.TI 7.1.8. Themes were identified, and storyboards that reflected the voices and stories of the respective communities were produced. An advisory committee reviewed the storyboards and provided additional comments and suggestions. The themes, comments and suggestions were incorporated into the films, which told the real stories of stroke as seen and felt by the community members.

### Church setting

In 2004, the Office of Minority Health of the NYC Department of Health formed the Borough of Brooklyn Ecumenical Advisory Group (BBEAG), comprised of 506 faith-based organizations (FBO) in Brooklyn. In 2006, the BBEAG formed the Borough of Manhattan Ecumenical Advisory Group (BMEAG), whose membership includes 100 FBOs. The mission of both groups is three-fold: (1) to serve as an advocate and conduit to eliminate and prevent health disparities, (2) to promote wellness to the residents of Manhattan and Brooklyn through health education and health outreach, and (3) to broaden health care access and services in partnership with the Office of Minority Health. These ecumenical networks provided support for the acceptance and promotion of the intervention and the recruitment of 14 study churches from our target communities.

### Church champions

Community involvement and ownership are important elements of a successful and sustainable intervention. As such, we will also recruit one member of each congregation to serve as the project church champion. Church champions will work with the RAs to schedule recruitment and study implementation events at the church. Church champions will also deliver informal stroke film screenings to all congregants following the completion of the 1-year formal data collection period. Church champions will receive $60 for their overall assistance and participation. To show our appreciation as well as keep them engaged in the project, the research team will also plan small social events or occasional gifts for the champions and other church administration that provide assistance with the implementation of the TASHE study.

### Study procedures

#### Church recruitment and randomization

Recruitment will occur first at the church level, then the participant level. Randomization will occur at the church level to prevent contamination and other threats to internal validity through interactions between members of the same church. Once a church agrees to participate, signs a covenant of agreement and identifies a church champion, they will be randomized to either the intervention or UC arm. The randomization sequence will be generated by the study statistician at a site away from the churches, in accordance with the CONSORT guidelines.

To be included in the study, churches must have at least 250 active members (we defined “active” as members who attend church weekly). The 14 churches will be randomly assigned to either the intervention (*N* = 7) or the usual care (*N* = 7) conditions, with 25 participants recruited and enrolled at each church. We estimate the prevalence of traditional stroke risk factors (such as hypertension) in these churches to pattern that of NYC population, which is 38% among Blacks and 30% among Hispanics, based on the 2012 NYC Department of Health Community Health Survey. In the event that fewer eligible participants are identified at specific churches than we anticipate, additional churches will be added as necessary. Each church will receive a $1000 donation as compensation for their time and space needed during the study period.

### Participant recruitment

Participants will be recruited from the church congregation. Following randomization of the churches, church personnel will assist the RA in organizing recruitment events after church services, where the research team will present the study and explains the rationale, significance and procedures. The RA will coordinate with the champion to determine space and convenient schedules for recruitment events as well as participant interviews. RAs will host blood pressure screening events where interested potential participants can have their blood pressure taken and learn more about the study. If interested, potential participants will receive an explanation of the study. Informed consent will be obtained from each participant. Participants will then be contacted the following week to schedule their eligibility screening and baseline interview.

Potential participants must meet certain inclusion criteria in order to be eligible for participation. Inclusion criteria include: (1) no prior history of stroke, (2) high risk – defined as a history of one or more stroke risk factors: hypertension, diabetes, tobacco use, abdominal obesity, heart disease and/or high cholesterol, (3) aged 34 years or older (due to the large increase in stroke incidence among minority groups at age 34 [41]), (4) self-identifies as Black or Hispanic, (5) a regular congregant of the church (attends services at least twice a month), and (6) lives in a household with a telephone. Exclusion criteria include: (1) unable to give consent, (2) has a participation-prohibiting disability, (3) history of dementia, (4) terminal illness or other medical illness resulting in mortality in less than 1 year, (5) severe hearing impairment, and (6) planning to move out of NYC in the next 3 years.

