### Study intervention

#### Intervention condition

It is widely accepted in the health promotion literature that interventions are more effective when they are culturally appropriate [51]. Thus, we optimize the potential impact of the intervention by enhancing its cultural appropriateness through cultural targeting. Using a transdisciplinary approach, we produced two culturally tailored, 12-min films (English and Spanish versions) in the first phase of the study. To accomplish this critical component, we organized a team of cultural leaders from local Black and Hispanic churches, a stroke expert, community-based researchers with expertise in culturally appropriate interventions, behavioral scientists – including narrative communication experts – a specialist in theory of knowledge acquisition, and a professional filmmaker. The director of the film is a seven-time Emmy award winning writer and producer of entertainment media who has experience in stroke narrative productions. To address the major barriers in the cascade of events and behavioral responses that occur in the pre-hospital setting of acute stroke, the screenplay has five didactic goals: (1) communicate knowledge of stroke symptoms, (2) communicate the *range of severity* with which the symptom may occur – for example, a slight slurring of the speech should be enough to precipitate action, (3) communicate the therapeutic benefit of calling 911, (4) overcome barriers to calling 911, including the reluctance to go to the ED, and (5) overcome issues related to denial or embarrassment if symptoms turn out not to be serious.

At baseline, the RA will provide participants with a study letter and the stoke film DVD (either in Spanish or in English) and ask them to watch it at least twice at home. The RA will also invite them to the church for one formal, assembly-style screening of the film. The RA will coordinate with the church champion to determine space and convenient schedules for the group film viewing. Participants will be reminded of the time and location of the film screening beforehand via phone. If a participant is unable to attend the larger group film screening, the RA will schedule an individual screening at a time and place more convenient for the participant.

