### Power calculation for the secondary outcome (stroke symptom knowledge)

For this binary outcome, it is posited that the control group will improve by 6%, starting at 4% with knowledge, based on a composite score for correct answers to the five cardinal “suddens” symptoms [57]. Given randomization, the intervention group is posited to start at the same level and improve 24%, for a net improvement of 18%. The assumptions are: R =0.85 (reliability); g = 2 (group); cluster size = 18; ICC = 0.02; VIF = 1+ (clustersize-1)*ICC = 1.34. A sample size of 125 subjects per group will provide 80% power to detect a group difference in the rate of increased knowledge at 6 months, from a baseline rate of 4% to a desired level of 28%.

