### Secondary hypothesis

*Participants who receive the culturally tailored narrative film intervention will demonstrate greater stroke symptom recognition at 6 months and 1 year following the intervention compared to those in the usual care arm.* Binary outcomes (stroke symptom knowledge) will be examined using generalized estimating equations (GEEs) with a logit link. Because randomization is at the church level, with clustering, such models allow for modeling the correlation due to clustering and repeated measures. Stroke knowledge will be coded as knowledgeable or not, based on predetermined cut scores. Baseline knowledge will be included in the model. Results can be converted to odds ratios. In the event that the above described logit analyses indicate one or more sources of potential bias, the predicted values of those analyses will be included as covariates in the a multilevel logistic regression model (SAS, version 9).

Prior to analyses, baseline values of all variables from each arm will be examined; however, no *p* values will be provided, and covariates are not proposed for inclusion in the main analyses of treatment effects. If one or more sources of potential (selection or attrition) bias are identified, the predicted values from those analyses will be included as covariates in secondary analyses. Depending on the severity of missing data, other modeling techniques may be used.

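### Participants are recruited after their church has been randomised, with no masking stated, so which members enrol may depend on the arm

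*Protocol article*

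**What the plan says.** **Order of events.** Under Church recruitment and randomization: "Recruitment will occur first at the church level, then the participant level". Once a church has agreed, signed its covenant and named a champion, "they will be randomized to either the intervention or UC arm". Under Participant recruitment: "Following randomization of the churches, church personnel will assist the RA in organizing recruitment events after church services". Consent, eligibility screening and the baseline interview all come later.

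**Who recruits, and what else they do.** Under Church champions: "Church champions will work with the RAs to schedule recruitment and study implementation events at the church". Under Intervention condition, for film churches only: "The RA will coordinate with the church champion to determine space and convenient schedules for the group film viewing", and "At baseline, the RA will provide participants with a study letter and the stoke film DVD". Under Control condition, the brochure is given out when the baseline interview ends.

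**Concealment.** The only measure stated is that the statistician generates the church sequence away from the churches.

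**Analysis.** Under Primary hypothesis, change in STAT is modelled and the Group × Time interaction is the primary test. Under Secondary hypothesis, "covariates are not proposed for inclusion in the main analyses of treatment effects". If selection or attrition bias is identified, covariates enter secondary analyses. The secondary-outcome power section assumes equal starting levels: "Given randomization, the intervention group is posited to start at the same level".

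**The concern.** In a cluster trial, randomising clusters balances, in expectation, whatever exists in the clusters at that moment. It balances the enrolled individuals only if they were identified beforehand, or if those who recruit and those who volunteer cannot act on the arm. Here the individuals come forward afterwards. An RA or champion who knows whether the church will get a film or a brochure may promote the study differently, and members who learn what is on offer may volunteer for different reasons.

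The two arms could then hold people who differ in motivation, in willingness to return, or in how readily they respond to health education. Such differences can appear as a difference in change over time, which is what the primary test measures. Adjustment afterwards cannot be relied on to remove them, because motivation and responsiveness are not among the planned measures.

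**Working it through.** **1. Sequence.** The section on church recruitment and the section on participant recruitment agree: church agreement, then allocation, then recruitment events, consent, screening and baseline. The order is explicit and does not depend on detail that a fuller protocol might add.

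**2. Can the arm be known during recruitment?** This is an inference from duties.
- Materials are handed over at baseline in both arms, so whoever does this must know the arm by a church's first baseline visit. If the same RA goes on recruiting there, the rest of that church's recruitment is done with the arm known.
- The champion helps to schedule recruitment and, in film churches only, the group viewing.
- Visits and payments differ (Retention section). Film: 30 + 3 × 15 = $75. Control: 30 + 2 × 15 = $60. A candidate told the full schedule before consenting could infer the arm.

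**3. The plan's own figures.** Inputs from the sample size section: σ = 17.83, ρ = 0.6, R = 0.85, VIF = 1 + 17 × 0.02 = 1.34, two-sided α = 0.05, power 0.80.

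n per group = 2 × [σ(1.960 + 0.842)/δ]² × (1 − ρ²) × VIF / R

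- δ = 8, 9, 10 gives 78.7, 62.2, 50.4 (Table 1: 79, 62, 50).
- n = 75, 100, 125 gives δ = 8.19, 7.10, 6.35 (Table 1: 8.19, 7.10, 6.34).
- Power at 125 per group for 8 points is 94% (stated: above 80%).

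The figures reproduce. The formula is not uniquely identified, because a plain endpoint comparison without VIF, ρ or R gives nearly the same numbers (78, 62, 50).

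**4. Standard error of the group contrast at 125 per group.**
- Baseline-adjusted form: 17.83 × √[(2/125) × 0.64 × 1.34/0.85] = 2.27 points.
- Change-score form: 17.83 × √[(2/125) × 2(1 − 0.6) × 1.34/0.85] = 2.53 points.

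**5. Illustration of bias.** Let differential enrolment shift the contrast by b points with no true effect. The value of b is an assumption, since the documents give none.

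Rejection rate = 1 − Φ(1.96 − b/SE) + Φ(−1.96 − b/SE)

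| b (STAT points) | SE 2.27 | SE 2.53 |
|---|---|---|
| 0 | 5% | 5% |
| 1 | 7.3% | 6.8% |
| 2 | 14.3% | 12.4% |
| 3 | 26.3% | 22.0% |
| 4 | 42.3% | 35.2% |

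A larger sample does not help: SE falls and b does not.

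**6. A baseline STAT gap does not determine b.** Suppose the enrolled groups differ by g at baseline.
- If each group stays at its own level, the follow-up difference is also g. The change contrast is g − g = 0. Adjusting for baseline then gives g − 0.6g = 0.4g, which is bias that the change analysis does not have.
- If both groups drift to a common mean, the follow-up difference is 0.6g. The change contrast is then off by 0.4g, and baseline adjustment removes it.

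The documents do not say which case applies, so neither b nor the better adjustment can be derived from a baseline gap.

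**The case against.** Much of the case on the other side stands. Nowhere does the article say that RAs or champions are told the arm while recruiting, and masking procedures or a recruitment script may be in a fuller protocol. Eligibility criteria and the baseline interview are the same in both arms. The pool is narrower than the minimum of 250 active members suggests, because entrants must be at least 34, have a stroke risk factor, have had no stroke and identify as Black or Hispanic. The primary analysis works on change from baseline, the secondary model includes baseline knowledge, and secondary analyses are foreseen if selection bias is found. The statement about equal starting levels is a power assumption for the secondary outcome and does not show how the primary outcome is analysed.

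These points limit what can be claimed, but they do not change the order of events. Common criteria restrict who may enter, not who among the eligible comes forward. A change analysis removes a stable baseline gap, not a difference in responsiveness.

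Two stronger readings are tempting. A reader might infer that randomisation no longer protects the comparison at all. That goes too far, because allocation between churches remains random and only enrolment within churches is exposed. A reader might also turn an assumed baseline gap into a false-positive rate through regression to the mean, as (1 − ρ) × gap. That needs both arms to regress to a common mean. STAT is first measured after consent and screening, so nobody can be selected on the observed score, and a stable gap between differently composed groups gives no spurious Group × Time effect.

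**Conclusion.** The point holds as a design weakness. Participants are recruited after allocation by people who may know the arm, no masking at that stage is stated, and randomisation does not protect which members of each church enrol. Differences by arm in motivation or responsiveness can therefore bias the Group × Time contrast.

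The size of the bias cannot be derived from the documents. The only quantitative statement available is conditional: a 2-point shift with no true effect would raise the rejection rate from 5% to about 12% to 14%. This rests on the plan's own SD, correlation, reliability, VIF and 125 per group, on a normal approximation, and on an assumed shift.

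No contradiction or arithmetical error in the plan is shown. The change is a cheap improvement, and it has most value for churches where recruitment has not begun.

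**What to change.** **Churches not yet randomised or opened.** Complete consent, eligibility screening and baseline interviews for the church's participants before the statistician releases its allocation to staff, champion or congregants. Then deliver the DVD or brochure. The Follow-up interviews section starts the control clock at the baseline interview; move it to brochure delivery. The film clock already starts at the in-church screening and need not change.

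**Churches already randomised.** Recruitment had begun by the time of the article (Trial status), so the order cannot be reversed there. Report by arm the numbers approached, eligible and consented, together with baseline STAT. Present a baseline-adjusted analysis beside the change analysis as a sensitivity analysis, not as a repair: step 6 of the working shows that adjustment can remove bias or add it. Adjusting for church language or ethnicity does not address this problem either, since these are attributes that the church had before randomisation.

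**Cost.** One additional contact or mailing per participant, a short delay before materials arrive, and a re-anchored control follow-up. No extra participants are needed.
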